## Abstract

**Background:**

With roughly 45,000 adult patients each year, distal radius fractures are one of the most common fractures in the emergency department. Approximately 60% of all these fractures are displaced and require surgery. The current guidelines advise to perform closed reduction of these fractures awaiting surgery, as it may lead to post-reduction pain relief and release tension of the surrounding neurovascular structures. Recent studies have shown that successful reduction does not warrant conservative treatment, while patients find it painful or even traumatizing. The aim of this study is to determine whether closed reduction can be safely abandoned in these patients.

**Methods:**

In this multicenter randomized clinical trial, we will randomize between closed reduction followed by plaster casting and only plaster casting. Patients aged 18 to 75 years, presenting at the emergency department with a displaced distal radial fracture and requiring surgery according to the attending surgeon, are eligible for inclusion. Primary outcome is pain assessed with daily VAS scores from the visit to the emergency department until surgery. Secondary outcomes are function assessed by PRWHE, length of stay at the emergency department, length of surgery, return to work, patient satisfaction, and complications. A total of 134 patients will be included in this study with follow-up of 1 year.

**Discussion:**

If our study shows that patients who did not receive closed reduction experience no significant drawbacks, we might be able to reorganize the initial care for distal radial fractures in the emergency department. If surgery is warranted, the patient can be sent home with a plaster cast to await the call for admission, decreasing the time spend in the emergency room drastically.

**Trial registration:**

This trial was registered on January 27, 2023.

## Administrative information

Note: the numbers in curly brackets in this protocol refer to SPIRIT checklist item numbers. The order of the items has been modified to group similar items (see http://www.equator-network.org/reporting-guidelines/spirit-2013-statement-defining-standard-protocol-items-for-clinical-trials/).

## Introduction

### Background and rationale {6a}

Each year, almost 26,000 adults are treated for a displaced distal radius fracture (DRF) in the Netherlands, making it one of the most common fractures in the ED [1–4]. According to a Swedish study, approximately 60% (= 16,000) of all DRFs are displaced [5]. The majority of all displaced DRFs are treated with osteosynthesis. This surgery is semi-acute planned operative care, mostly within the first week after trauma.

The Dutch DRF guidelines advise to perform closed reduction (CR) of displaced DRFs awaiting surgery at the ED, because it may lead to post-reduction pain relief, and a successful reduction may warrant conservative treatment [6]. Techniques used for CR of DRFs are manual traction and finger-trap traction [7]. Both procedures are often painful despite injection of a local anesthetic between the fracture fragments [8–10]. Sometimes, the patient is even sedated (as well). Besides the physical discomfort associated with CR, patients may experience CR as a traumatizing event as well. This questions how relevant CR at the emergency department really is. The same guideline also acknowledges that evidence supporting the advice to perform a CR is lacking [11, 12]. Meanwhile, CR is a painful, costly, time-consuming procedure, often requiring anesthesia and most surgeons experience a substantial re-dislocation at surgery.

Furthermore, the guideline suggests that good fracture alignment justifies conservative treatment. This recommendation is based on three rather outdated randomized studies comparing cast immobilization with either external fixation of the wrist or percutaneous pin fixation [13–15]. However, both surgical techniques have been largely replaced by internal plate fixation. Recent European randomized controlled trials have shown that in displaced DRFs, despite acceptable fracture reduction, volar plating is superior to cast immobilization in terms of functional outcome, quality of life, and prevention of secondary dislocation [16–18]. This was also concluded in a large meta-analysis of 23 trials including 2254 patients, published last year [19]. Opposed to the current but rather old guideline, strong recent evidence suggests that operative treatment is preferred over conservative treatment in adult patients with displaced DRFs. A trend towards more operative treatments is expected and makes our research question more relevant.

### Objectives {7}

The aim of this multicenter, randomized clinical trial is to determine if CR in patients with a displaced DRF can be safely abandoned before the plaster cast, as a bridge to surgery, is applied.

### Trial design {8}

This trial is designed as a non-inferiority multicenter cluster randomized trial. Participants will be equally distributed between the two treatment arms.

## Methods: participants, interventions, and outcomes

### Study setting {9}

The study will be situated at six public hospitals in and round the city of Rotterdam. All participating hospitals are part of the BeterKeten foundation that provided the research grant. The group consists of both rural and academic- and city-centered hospitals.

### Eligibility criteria {10}

All patients aged between 18 and 75 years with a displaced distal radius fracture requiring surgery will be approached. A DRF is considered displaced with an indication for surgery if one of the following criteria is met:Articular gap or step-off ≥ 2 mm. The intra-articular gap is defined as the maximal distance between fracture fragments parallel to the articular surface. The intra-articular step-off is defined as the maximal distance between fracture fragments perpendicular to the articular surface [16]Carpal alignment > 5 mm. The carpal alignment represents the length of a perpendicular line between a line along the inner rim of the volar cortex of the radius and the center of the capitate [18]Dorsal angulation > 10°, volar angulation > 20°. The dorsal/volar angulation represents the angle between a line that connects the dorsal and volar rim of the distal radius and a line perpendicular to the longitudinal axis of the radius [20]Radial height loss > 3 mm. Also known as the radial length, defined as the distance between two lines, both perpendicular to the long axis of the radius. One line goes through the tip of the radial styloid, and the second goes through the most distal point of the ulnar head [21]Radial inclination < 15°. The radial inclination is the angle between two lines. One line connects the radial styloid process with a point on the ulnar aspect of the distal radius, in the center between the dorsal and volar rim. The second line is directed perpendicularly to the longitudinal axis of the radius [20]Coronal plane translation. This term is used to describe radial displacement of the distal fragment. Radial translation of the distal fragment might be associated with DRUJ instability due to lack of tension on the distal oblique bundle (the most distal part of the distal interosseous membrane) and the pronator quadratus. Coronal plane translation can be measured by drawing a line on the ulnar side of the radius which intersects the lunate. The point of intersection within the lunate is evaluated by drawing a second line along the transverse width of the lunate parallel with the distal joint. In a normal situation, the lines should bisect at 50% [22, 23]Incongruent DRUJ: the ulnar side of the distal radius and radial side of the ulna should converge in the form of a Gothic arc. This arc should not be interrupted

The criteria for exclusion are:Patients younger than 18 years or older than 76 years oldAcute limb threatening ischemia, defined as: “any sudden decrease in limb perfusion causing a potential threat to limb viability” [24]Skin tenting or symptoms that suggest an impending open fractureAcute symptoms of median nerve compression, such as paresthesia in digit 1–3, or extending to the entire hand, pain, hand weakness, and cramps in the hand [25]Other fractures in the same or other upper extremity which require a separate treatmentPrevious distal radius fracture in the ipsilateral wrist < 3 monthsMultiple trauma patients (Injury Severity Score (ISS) ≥ 16)Patients with impaired wrist function due to previous injuries, bone disorders, or neurological disordersInsufficient comprehension of the Dutch language to understand a rehabilitation program and other treatment information as judged by the attending physicianInability to complete the study period (i.e., patients from abroad who will have surgery outside one of the participating hospitals)

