**Fig. 2 Fig2:**
[figure not shown]
Power curve for simulation 2 assuming unbalanced clusters (unequal number of patients included per center) and adjustment for seasonal effects

In the Maasstad Hospital, approximately 590 adult patients are diagnosed with a DRF per year. According to Brogren and colleagues, approximately 350 (60%) will be displaced [5].

However, not all of these patients will have CR followed by surgical treatment. Assuming that 60% of all patients with a displaced DRF will meet the inclusion criteria, combined with a rejection rate of 30%, we estimate to require 13 months for inclusion in case of a single-center design. Assuming that the average amount of inclusions per month in the other participating centers equals the amount in the Maasstad Hospital, we can divide the required time by the amount of centers. With a total of six participating centers, we estimate to require 3 months to complete the inclusion. Combined with a follow-up time of 12 months and 3-month margin, the total required time for the clinical part of the trial will be 18 months.

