### Implementation {16c}

The primary investigator generated the allocation sequence. Patients are enrolled by attending physicians in all participating hospitals. With the cluster randomization, every hospital will know beforehand what intervention to assign.

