## Discussion

The main practical issue we focus on during this trial is the decision of the attending trauma surgeon whether or not the fracture requires surgical fixation. We trust all participating physicians adhere to the national guidelines, but practice shows at least some amount of inter-observer variability, with several cases of initial conservative treatment, with the intention of avoiding surgery. To monitor this, all exclusions that were eligible for inclusion according to the stated criteria will be kept track of, including the reason for exclusion.

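### The eligibility criteria do not say whether displacement and surgical indication are judged before or after reduction, so in reduction periods only, a good reduction could remove a patient before enrolment

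*Protocol article*

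**What the plan says.** The Eligibility criteria section lists radiographic thresholds (gap or step-off, carpal alignment, angulation, radial height, inclination, coronal translation, distal radioulnar congruence) and says "A DRF is considered displaced with an indication for surgery if one of the following criteria is met". It does not say which film is read. The abstract's Methods describe patients "presenting at the emergency department with a displaced distal radial fracture and requiring surgery according to the attending surgeon", and give no time for that judgement.

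The Background reports two features of the Dutch guideline: it advises closed reduction partly because "a successful reduction may warrant conservative treatment", and "the guideline suggests that good fracture alignment justifies conservative treatment". The authors dispute this position. The closing Discussion nevertheless says, of the decision whether a fracture needs surgery, "We trust all participating physicians adhere to the national guidelines". It adds that practice varies, "with several cases of initial conservative treatment, with the intention of avoiding surgery". Its remedy is a log of patients who met the criteria but were excluded, with the reason.

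Each hospital delivers one treatment and changes to the other halfway (Sequence generation), and "every hospital will know beforehand what intervention to assign" (Implementation). Recruitment places the eligibility check and consent in the emergency department, followed by baseline recording, and does not mention reduction. The primary outcome is mean daily VAS pain from the emergency visit to surgery (Outcomes).

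**The concern.** Reduction is meant to change the alignment on which most of these criteria rest. Only reduction periods produce a post-reduction film; in the other periods the presenting film is the only one. If a site reduces first and judges afterwards, or if a good result leads it to withdraw the surgical indication before enrolment, the same written criteria select two different populations within one hospital.

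This can happen without any conscious selection, so it is separate from the open allocation. Randomising the order of periods, the crossover and a random centre effect do not remove it, because the filter acts after the allocated treatment has been given. At stake is whether the two arms are comparable on the primary outcome, in a trial that tests a non-inferiority margin of 9.7 mm.

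**Working it through.** **1. Is the order fixed anywhere?**

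- Eligibility criteria: thresholds in detail, no film and no time point.
- Abstract, Methods: displacement is mentioned at presentation; the surgeon's judgement is untimed.
- Objectives: reduction is a step before the cast, as a bridge to surgery. This implies that surgery is already intended, but sets no recording rule.
- Recruitment: eligibility, consent, baseline, in about 30 minutes. Reduction takes place in the same department, so naming the department does not settle the order.
- Background and closing Discussion together: the guideline that physicians are trusted to follow lets a good reduction replace surgery.

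The text leans towards assessment at presentation but does not require it.

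**2. Does the log close the gap?** It covers patients eligible under the stated criteria. If those are read after reduction, a well-reduced fracture is not eligible and need not be logged. If they are read before, the log reveals the loss but does not prevent it.

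**3. The plan's own figures.** Inputs from the Sample size section: margin 9.7 mm (half of 19.3 mm), SD 15 mm, two-sided alpha 5%, power 80%, loss 10%.

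- Normal approximation per arm: 2 × 15² × (1.960 + 0.842)² / 9.7² = 37.5, so 38, or 76 in total. The t-based version, with the hospital effect cancelled by the crossover, gives 78, against the plan's 80.
- 120 / 0.9 = 133.3, so 134, as stated.

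The sample size is not in question.

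**4. Size of a possible bias (assumed inputs).** Let f be the share of eligible fractures lost in reduction periods, and d the amount by which their mean VAS lies below that of the patients kept. Write K for the mean of those kept.

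Bias = K − [(1 − f)K + f(K − d)] = f × d.

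The standard error implied by the plan's 80% power is 9.7 / (1.960 + 0.842) = 3.46 mm. With a shift b = f × d:

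- one-sided error at a true difference of 9.7 mm = Φ(b / 3.46 − 1.960);
- power at a true difference of 0, if the sign is reversed = Φ((9.7 − b) / 3.46 − 1.960).

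| f | d (mm) | Shift (mm) | Share of margin | Error (nominal 0.025) | Power if sign reversed (nominal 80%) |
|---|---|---|---|---|---|
| 10% | 5 | 0.5 | 5% | 0.035 | 76% |
| 20% | 10 | 2.0 | 21% | 0.083 | 60% |
| 30% | 10 | 3.0 | 31% | 0.137 | 49% |
| 40% | 15 | 6.0 | 62% | 0.410 | 19% |

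No value of f or d, nor the sign of d, comes from the article. The table shows sensitivity and is not an estimate.

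**The case against.** The strongest reply is that the article already implies assessment at presentation. The abstract ties displacement to arrival, the Objectives treat reduction as a bridge to a planned operation, Recruitment runs from eligibility to consent to baseline, and a VAS is taken before the plaster. No section describes a site reducing first and screening afterwards. The authors also reject the guideline's view of successful reduction, set thresholds of their own, and name the surgical decision openly as their main practical issue, with a log. And a condensed article may leave operational detail to the full protocol.

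Much of this stands: the consequence is a risk, and the intended order is probably the sensible one. It does not dispose of the point. None of these sections puts indication and consent before reduction, and the conflict between the Background and the closing Discussion lies in the published text. Many physicians in six emergency departments, at all hours, apply these criteria.

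A reader might go further and infer from the recruitment projection in the Sample size section ("not all of these patients will have CR followed by surgical treatment") that the trial recruits a post-reduction population. That sentence only discounts annual volume for feasibility; it defines neither eligibility nor screening order, and half of the trial receives no reduction.

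**Conclusion.** The point holds as a moderate risk of differential selection. The article leaves the eligibility time point open and relies on a guideline under which a good reduction may cancel surgery, so in reduction periods only, the allocated treatment can filter entry.

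A reader might infer that the reduction arm will in fact lose its less painful fractures and that non-inferiority will be declared falsely. The documents do not support that. They report several cases of initial conservative treatment, but no rate, no breakdown by period and no pain data. Under the assumption that the patients lost have less pain, a 3 mm shift would take up 31% of the margin and raise the one-sided error from 0.025 to 0.137. Under the opposite assumption, the same shift would lower power from 80% to 49%. Both figures rest on the assumed f and d and on the standard error implied by the planned power.

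**What to change.** Reconcile the abstract's Methods, Background, Eligibility criteria, Recruitment and closing Discussion around one entry point:

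- State that all eligibility criteria are assessed on the presenting radiograph.
- Record the surgical indication and consent, with the time, before the allocated intervention, identically in both periods.
- Use the same definition for the log of eligible patients not included, and report the log by period.
- Keep every included patient in the primary analysis whatever the alignment after reduction, and state where the pain window ends for a patient who is not operated on, since it now runs until surgery.

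Further treatment stays with the surgeon; the change fixes only who counts as enrolled, and when. A separate exclusion for fractures already reduced is not needed for this purpose.

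The cost is a sentence or two in the eligibility text and a time field on the inclusion form; the total stays at 120, or 134 with loss. The downside is that a few included patients may not be operated on, and their diary data must still be counted. Trial status reports the first inclusion in June 2023, so for patients already enrolled the order of film, indication, consent and reduction should be retrieved from hospital records where possible.

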### Who will take informed consent? {26a}

Informed consent will be obtained by the attending physician at the emergency department. All physicians will be either trained in the protocol or supervised by someone who is.

### Additional consent provisions for collection and use of participant data and biological specimens {26b}

There is a separated section on the informed consent form where participants can check a box to give consent for the use of date for ancillary studies. This trial does not involve collecting biological specimens for storage.

## Interventions

### Explanation for the choice of comparators {6b}

This trial will compare closed reduction prior to surgery in displaced distal radial fractures to no closed reduction prior to surgery. Currently, the Dutch guidelines state there is a knowledge gap concerning the efficacy of closed reduction prior to surgery. Therefore, either outcome of this study would lead to an update of said guideline. In daily practice, both treatments are used at the moment of writing this protocol.

### Intervention description {11a}

Closed reduction of distal radial fractures is performed with axial traction on the wrist with Chinese finger traps connected to weights, with manipulation by the caretaker of a combination of both. In most cases, a local anesthetic will be administered in the form of hematoma block with lidocaine between fracture fragments [7].

### Criteria for discontinuing or modifying allocated interventions {11b}

If patients allocated to the no closed reduction group develop neurovascular symptoms, the attending physician can opt to perform closed reduction regardless to relieve said symptoms.

### Strategies to improve adherence to interventions {11c}

Intervention will or will not be performed in the emergency department, so no additional strategies are required.

### Relevant concomitant care permitted or prohibited during the trial {11d}

Apart from the closed reduction, patients will receive standard care and have no trial specific limitations.

### Provisions for post-trial care {30}

Standard test subjects’ insurance has been taken out for all participants.

### Outcomes {12}

The primary outcome is the average of the pre-operative visual analog scale for pain (VAS) score, reported on a daily basis from the ED visit until surgery.

Secondary outcomes are wrist function measured with the Patient-Rated Wrist Evaluation (PRWE) score after 6 weeks and 3, 6, and 12 months, length of stay in the ED, type and quantity of used pain medication, patient satisfaction, quality of life, and complications. Furthermore, a cost-effectiveness analysis will be performed using the Medical Consumption Questionnaire (iMCQ) and Productivity Cost Questionnaire (iPCQ) [26, 27], and the ability to assess CT scans of unreduced fractures and reduced fractures will be compared.

### Participant timeline {13}

The participant timeline is shown in Table 1.

**Table 1 Tab1:** Overview questionnaires

Name	Follow-up moment	Time spent per visit (minutes)	Time spent in total (minutes)
Listen, read and complete informed consent	ED	15	15
Pain diary	Every day until surgery	5	5 × 7–14* = 35–70
PRWE	6 weeks, 3 months, 6 months, 12 months	5	20
EQ-5D-5L	6 weeks, 3 months, 6 months, 12 months	5	20
ROM + grip strength	6 weeks, 3 months	1	2
Report used health resourced	6 weeks, 3 months, 6 months, 12 months	2	8
Report pain medication	6 weeks, 3 months, 6 months, 12 months	2	8
		**Total**	110–145

*Surgery usually takes place between 7 and 14 days

### Sample size {14}

The sample size calculation is based on our primary outcome parameter: the VAS score for pain reported on a daily basis from the visit to the ED until the day of surgery. To find out if the pre-operative pain scores of patients that are refrained from CR are comparable with the scores of the CR group, we will use a non-inferiority test. This requires a non-inferiority margin, which is the biggest difference between the two groups in favor of the CR group, without a statistical difference [28]. The European Medicines Agency advices to base the non-inferiority margin on a difference that is not clinically important [29]. Therefore, our non-inferiority margin is 50% of the minimal clinical important difference (MCID) of the VAS [28]. Based on a systematic review concerning the MCID of VAS scores, a MCID is a context-specific and methodological dependent value [30]. To the best of our knowledge, the MCID of the VAS score for DRFs is unknown. Therefore, we used the MCID of a study that included trauma patients with isolated acute extremity pain [31]. For the description of the MCID of the VAS score, the VAS scale is seen as a 100 mm line. With an MCID of 19.3 mm, our non-inferiority margin will be 9.7 mm (= 50%). As only Bird et al. provide a standard deviation (SD) around the MCID, we will use that value of 15 mm for our sample size calculation [24]. To correct for a cluster-effect we use an intra-cluster correlation (ICC) coefficient between the different hospitals of 0.06, which is generally reported in the literature for hospital processes. To calculate the required sample size, two simulations were run both assuming a fixed number of six clusters (hospitals). In the first simulation, an equal number of subjects per hospital was assumed. Hospitals were randomized to start with treatment A (3 centers) or B (3 centers) in a 1:1 fashion and crossed over after half of the patients were included. For total sample sizes varying from 12 to 502 with increments of 12, 5000 simulations were run for each sample size considered. In each simulation, random data was generated under the specifications described above. A linear mixed model was fitted with a random intercept for cluster and treatment group as fixed effect. A 95% confidence interval was calculated based on the t-distribution with degrees of freedom estimated by the Satterthwaite method. The power was calculated as the percentage of simulations in which the upper limit of the 95% confidence interval was smaller than the non-inferiority margin. From the first simulation, it followed that, using a two-sided alpha of 5%, *n* = 80 patients total would be required in total to demonstrate non-inferiority with a power of 80% (Fig. 1).
